#### 6.1.2 *Left Ventricular (LV) Dimensions*

LVESD and LVEDD will be assessed pre-operatively (Assessment I), early post-operatively (Assessment III), after 6 months (Assessment V) and after 24 months (Assessment VI) by echocardiography.

Echocardiography will be performed in accordance with the Schedule of Assessments (see Table 2). The review will be done centrally by a reviewer blinded to the treatment received by the patient.

### 6.1.3 *Classification of Heart Failure (NYHA)/Angina (CSS)*

Patients will be graded according to the NYHA classification as follows:

- Class I: Patients with no limitation of activities; they suffer no symptoms from ordinary activities.
- Class II: Patients with slight, mild limitation of activity; they are comfortable with rest or with mild exertion.
- Class III: Patients with marked limitation of activity; they are comfortable only at rest.
- Class IV: Patients who should be at complete rest, confined to bed or chair; any physical activity brings on discomfort and symptoms occur at rest

NYHA assessments will be performed in accordance with the Schedule of Assessments (see Table 2). Additionally the CCS classification will be used to classify angina.

#### **Canadian Cardiovascular Society (CCS) classification system for Angina**

- CCS Class 0 Asymptomatic
- CCS Class I Ordinary physical activity such as walking, climbing stairs does not cause angina. Angina occurs with strenuous, rapid or prolonged exertion at work or recreation
- CCS Class II Slight limitation of ordinary activity. Angina occurs on walking or climbing stairs rapidly, walking uphill, walking or stair-climbing after meals, or in cold, or in wind, or under emotional stress, or only during the few hours after awakening. Walking more than two blocks on the level and climbing more than one flight of ordinary stairs at a normal pace and in normal conditions.
- CCS Class III Marked limitations of ordinary physical activity. Angina occurs on walking one to two blocks on the level and climbing one flight of stairs in normal conditions and at a normal pace.
- CCS Class IV Inability to carry on any physical activity without discomfort - anginal symptoms may be present at rest.

### 6.1.4 *Heart Catheterization*

Critical stenosed vessels ( $\geq 50\%$ ) will be recorded in the CRF as follows: LMCA, RIVA, RCX, RCA. The LVEF (%) and area of LV infarction (septal, posterior, anterior, lateral and other) will also be recorded in the CRF (Assessment I, Screening). Historic data (not older than 3 months) may be used.

Quality will be recorded as akinetic, hypokinetic, hypokinetic to akinetic or dyskinetic.

### 6.1.5 *Cardiac MRI Scan*

Cardiac MRI Scan will be performed in accordance with the Schedule of Assessments (Table 2, Assessments Screening, Hospital Discharge, 6-Month Follow-Up). The analysis and interpretation of data from the cardio MRI concerning LV function parameters will

be performed centrally by a reviewer blinded to the treatment the patient has received. The value for LVEF for Assessment I/Screening will be determined within 12 hours by the MRI Core Lab personnel and the result will be forwarded immediately to the treating physician. The following will be recorded continuously in the CRF:

- Date of recording
- LV mass ( $\text{g/m}^2$ ), body surface ( $\text{m}^2$ ), weight (kg), height (cm)
- LVEDV, LVESV, LVEF (%), Scar tissue total (g), Non-viable tissue (g)
- Ventricle function and wall motion (quality) for segments 1-17 (see Figure 7; 1 = hyperkinetic, 0 = normokinetic, -1 = hypokinetic, -2 = akinetic, -3 = dyskinetic)
  - Wall motion thickening (%)
  - Regional muscle mass (g)
- Perfusion at stress and at rest for segments 1-17 (see Figure 7; 0 = normal, 1 = reduced subendocardial, 2 = reduced transmural)
- Vitality/late enhancement (LE) for segments 1-17 (see Figure 7); LE volume (% LV mass), transmural LE (%)
- Total assessment vitality for segments 1-17 (see Figure 7; 0 = normal, -1 = stunned, -2 = hibernating, -3 = infarct)
- Unwanted tissue changes; no/yes, if yes, describe
- Pericardial effusion (no, few, moderate, much)
- Pleural effusion (no, few, moderate, much)
- Thrombus no/yes

## Left Ventricular Segmentation

[figure not shown]

- |                        |                       |                     |
|------------------------|-----------------------|---------------------|
| 1. basal anterior      | 7. mid anterior       | 13. apical anterior |
| 2. basal anteroseptal  | 8. mid anteroseptal   | 14. apical septal   |
| 3. basal inferoseptal  | 9. mid inferoseptal   | 15. apical inferior |
| 4. basal inferior      | 10. mid inferior      | 16. apical lateral  |
| 5. basal inferolateral | 11. mid inferolateral | 17. apex            |
| 6. basal anterolateral | 12. mid anterolateral |                     |

**Figure 7: Left ventricular segmentation**

#### 6.1.6 *Echocardiography*

Echocardiography will be performed as additional parameter to MRI in accordance with the Schedule of Assessments (Table 2, Assessments I, III, V, VI: Screening, Hospital Discharge, 6-Month Follow-Up (FU), 24-Month FU). The analysis and interpretation of data from the echocardiography concerning LV function parameters will be done centrally by a reviewer blinded to the treatment the patient has received. The date of performance will be recorded in the CRF. The heart rate (per min) and the quality of the images will be documented: good, middle, bad, orthograde ultrasound not measurable. LVEDD (mm), LVEDV (cm^3), LVESD (mm), LVEF (%; four chamber view), IVSD (mm), LVPWD (mm) and LVOT (mm) will be recorded in the CRF. The main area of impaired LV infarction will be recorded in the CRF. Quality assessment of wall movement will be recorded as normal, akinetic, hypokinetic or dyskinetic and the presence of an aneurysma. Pericardial effusion will be assessed: no/yes, if yes: document size (mm) and location (anterior, posterior, lateral, circular).

Furthermore the following has to be documented:

- Mitral regurgitation (none, mild, moderate)
- Tricuspid regurgitation (none, mild, moderate; if mild or moderate:  $\Delta$  Pmax in mm/Hg)
- Transmittal flow: VE in cm/sec, VA in cm/sec, VE/VA < 1 or > 1; DT (VE) in msec), VTI (LVOT) in cm
- Aortic valve regurgitation (none, mild, moderate), RVEDD (RVOT) in mm, LA (left atrium) in mm, RA (right atrium, 4 CV) in mm
- Unwanted tissue changes; no/yes; if yes, describe

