### 4.2 Exclusion Criteria

Patients will be entered into this study only if they meet none of the following criteria:

1. Emergency operation
2. Presence of any moderate-severe valvular heart disease requiring concomitant valve replacement or reconstruction
3. Medical History of recent resuscitation in combination with ventricular arrhythmia classified by LOWN  $\geq$  class II
4. Acute myocardial infarction within last 2 weeks
5. Debilitating other disease: Degenerative neurologic disorders, psychiatric disease, terminal renal failure requiring dialysis, previous organ transplantation, active malignant neoplasia, or any other serious medical condition that, in the opinion of the Investigator is likely to alter the patient's course of recovery or the evaluation of the study medication's safety
6. Impaired ability to comprehend the study information
7. Absence of written informed consent
8. Treatment with any investigational drug within the previous 30 days
9. Apparent infection (c-reactive protein [CRP]  $\geq 20 \text{ mg/L}$ , fever  $\geq 38.5^\circ \text{C}$ )
10. Contraindication for MRI scan
11. Immune compromise including Anti HIV 1/2, HBsAg, Anti-HBc-IgG, Anti HCV, Treponema pallidum
12. Pregnant or breast feeding
13. Childbearing potential with unreliable birth control methods
14. Have previously been enrolled in this study, respectively phase I and phase II

15. Known hypersensitivity or sensitization against murine products and human-anti-mouse-antibody-titer  $\geq 1:1000$
16. Contraindication to bone marrow aspiration
17. Known hypersensitivity against iron dextrane

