### 6.3 Safety Parameters

#### 6.3.1 *Adverse Events (AEs)*

##### 6.3.1.1 *Definitions*

###### 6.3.1.1.1 Adverse Events

Any untoward medical occurrence in a patient or clinical investigation subject administered a pharmaceutical product and which does not necessarily have a causal relationship with this treatment is defined as an AE. An AE can therefore be any unfavorable and unintended sign (including an abnormal laboratory finding), symptom, or disease temporally associated with the use of an investigational medicinal product (IMP), whether or not related to the IMP.

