### 6.3.1.3 Monitoring, Recording and Reporting of Adverse Events

#### 6.3.1.3.1 General Requirements

During the course of the study, all AEs (including SAEs), irrespective of the relatedness to the study drug, will be recorded on the AE pages of the CRF. During each monitoring visit, the Investigator and the monitor will review all AEs. The Investigator will be

responsible for ensuring that correct information concerning all AEs is included on the appropriate CRF forms.

The following data will be recorded:

- description of the AE: nature, frequency, intensity, time and date of onset and resolution, treatment, outcome, and causal relationship (in the opinion of the Investigator) to the study drug for each AE;
- whether the AE has to be considered as a SAE;
- action taken.

All AEs occurring during the study must be followed-up until the AE has completely resolved, stabilized or the sequelae can be assessed by the Investigator. In case of withdrawal the respective CRF has to be completed.

The results of additional diagnostic measures as the result of an AE, such as laboratory tests, ECG, angiogram, echocardiogram and MRI must be available at site and eventually copied on request.

A flow chart for the reporting of SAEs is shown in Figure 8.

[figure not shown]

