#### *6.3.1.5 Adverse Events of Specific Interest*

Events that are listed in Appendix 2 are considered to be of specific interest for the purpose of this study and are monitored in detail. Documentation and reporting of Adverse Events of Specific Interest will be according to the standard procedure of SAE reporting in Section 6.3.1.3.2. continuously up to study end and furthermore as safety follow up to Assessment VI after 24 months. After study termination (Assessment V, 6-Month Follow-Up) AEs not listed as AEs of specific interest will not be documented unless they are possibly, probably or definitely related to the investigational medicinal product or result in death. In case of seriousness all possibly, probably or definitely related AEs will be reported at Assessment VI, 24-Month Follow-Up.

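### The echo grading of mitral, tricuspid and aortic regurgitation stops at moderate, also after surgery, so the echo data cannot show severe regurgitation as such.

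*Protocol*

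**What the plan says.** Section 6.1.6 sets one item list for every scheduled echocardiogram: "Table 2, Assessments I, III, V, VI: Screening, Hospital Discharge, 6-Month Follow-Up (FU), 24-Month FU". It introduces the valve items as things that have to be documented:

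- Mitral: "Mitral regurgitation (none, mild, moderate", and no further level.
- Tricuspid: "Tricuspid regurgitation (none, mild, moderate; if mild or moderate", in which case a pressure gradient is recorded.
- Aortic: "Aortic valve regurgitation (none, mild, moderate", and no further level.

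None of the three has a free-text option. The unwanted tissue changes item in the same list does have one.

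At entry, Section 4.2 excludes "Presence of any moderate-severe valvular heart disease requiring concomitant valve replacement or reconstruction".

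Outside the echo list, Section 6.3.1.3.1 states that "all AEs (including SAEs), irrespective of the relatedness to the study drug, will be recorded on the AE pages of the CRF", and Section 6.3.1.6 records reoperation, reintervention and readmission as yes or no at 6 and 24 months. For the time after the 6-month visit, Section 6.3.1.5 states: "AEs not listed as AEs of specific interest will not be documented unless they are possibly, probably or definitely related" to the investigational product or fatal. The 24-month visit list in Section 7.2.6.3 asks for any AE or SAE since the last assessment.

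**The concern.** A three-level scale may suit screening, where valve disease that needs a procedure is excluded. The same scale is then used after surgery and injection, when no entry criterion limits what can be found. Its top level is not the worst possible finding, so the worst finding has no correct entry.

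What is at stake is the resolution of the safety data. Section 8.2 calls for frequency tables by treatment group for the data reported in the CRF. In such tables severe regurgitation would either sit inside the moderate row or be counted as missing, and Section 8.2 says that missing values are not replaced. A difference between arms that lies only in severe versus moderate regurgitation would not appear.

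**Working it through.** The protocol gives no figure on this point, so the check sets its sections side by side and counts.

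**1. Is the missing level a slip in one line?** It is unlikely. All three valves have the same three levels, and the tricuspid condition names mild and moderate as the only levels above none.

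**2. How far does the gap reach?** There are 4 scheduled echocardiograms (Assessments I, III, V and VI), of which 3 are post-operative. That makes 3 valves × 4 visits = 12 gradings per patient, of which 3 × 3 = 9 are post-operative. Assessment VI lies after data closure (Section 3.1), so 3 × 2 = 6 post-operative gradings fall within the study proper.

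**3. Which changes would the echo data misstate?** Take the true grade as none, mild, moderate or severe. There are 6 possible worsenings. If severe is entered as moderate:

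| True worsening | Recorded as |
|---|---|
| none to mild | none to mild |
| none to moderate | none to moderate |
| mild to moderate | mild to moderate |
| none to severe | none to moderate (understated) |
| mild to severe | mild to moderate (understated) |
| moderate to severe | no change (invisible) |

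Three of the 6 are recorded correctly, 2 are understated and 1 disappears. If severe is left blank instead, the last three become missing. This counts types of change, not patients.

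**4. Can a patient start at moderate?** Yes. Exclusion 2 removes moderate-severe disease only when it requires a concomitant valve procedure. A patient with moderate regurgitation that does not require one can be enrolled, and is then already at the top of the scale.

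**5. Does another scheduled examination grade the valves?** No. The MRI list in Section 6.1.5 has no valve item, and Table 2 schedules no MRI at 24 months.

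**6. Is there a route outside the echo list?**

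- *Up to 6 months: yes.* Section 6.3.1.1.1 is broad: "An AE can therefore be any unfavorable and unintended sign (including an abnormal laboratory finding), symptom, or disease". Section 6.3.1.3.1 requires such events to be described whatever their relatedness. A valve reoperation would be captured under MACE, without the grade of regurgitation.
- *This is not equivalent to a grading.* AE severity in Section 6.3.1.2.1 follows symptoms and need for treatment, so severe regurgitation without symptoms would be class I. Under Section 6.3.1.3.3, class I and II events are analysed at the end of the trial and classes III to V go to the Safety Monitoring Board. An AE entry also depends on someone reporting it, whereas the echo item is completed for every patient examined.
- *After 6 months: uncertain.* Section 6.3.1.5 keeps AEs of specific interest, related AEs and deaths. Appendix 2 contains no valve event. Section 3.1 describes the safety follow-up in similarly narrow terms. Section 7.2.6.3 says any AE or SAE. Whether an unrelated severe regurgitation found at 24 months is documented depends on which section the site follows.

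**The case against.** The strongest objection is that a reader might infer from the three-level scale that severe regurgitation cannot be recorded in this trial at all. The protocol does not support that. The AE definition and the duty to record all AEs up to 6 months give it a described entry. It becomes an SAE if it meets the seriousness criteria, MACE captures reoperation and reintervention, and left ventricular failure is followed to 24 months as an AE of specific interest. This stands, and it limits the point to the echo data.

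Other objections also carry weight:

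- Regurgitation grade is neither a primary nor a secondary endpoint (Section 3.2), and the synopsis safety list uses echocardiography only for unwanted tissue changes. This stands, and it keeps the point minor.
- If severe cases are entered as moderate, an excess of moderate-or-worse regurgitation in one arm would still show. This stands; the loss is within the top category. It does not hold if such cases are left blank.
- Section 1.3 lists deterioration of heart function as a risk, but the protocol measures that directly through LVEF, volumes, NYHA class and NT-proBNP, and does not tie it to valve function. This stands, so that risk is no basis for rating the point higher.
- The 24-month echocardiogram comes from a practice-based cardiologist after data closure. This stands as a qualification, but Section 6.1.6 still names that visit for the same list.
- The CRF is not shown and may offer more levels. This is possible; the point is about what the protocol prescribes.

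**Conclusion.** The point holds for the scheduled echo grading. As the protocol is written, severe mitral, tricuspid or aortic regurgitation cannot be graded as such in the echo data at discharge, 6 months or 24 months, and worsening from moderate is invisible there. It would be identifiable only through AE or MACE reporting, and after 6 months Sections 6.3.1.5 and 7.2.6.3 disagree on whether it would be documented.

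A reader might also take the size to be that every severe case is lost. Every severe case is misgraded or blank in the echo list, but that follows by definition from a scale without that level and says nothing about how many patients are concerned. The protocol gives no expected number, and it could be very small.

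The conclusion assumes that the CRF follows the list in Section 6.1.6. It has no bearing on the primary endpoint (LVEF by MRI), the sample size or the significance level. It is a minor improvement to the safety data.

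**What to change.** 1. In Section 6.1.6, add a severe level to the mitral, tricuspid and aortic regurgitation items at all visits.
2. Extend the condition for recording the tricuspid gradient so that it also covers severe.
3. Tabulate shifts in grade from screening to each later echocardiogram by arm, descriptively and without a test.
4. Reconcile Section 6.3.1.5 with Section 7.2.6.3, and Section 3.1 with both, so that it is clear which AEs are documented between 6 and 24 months.

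The cost is one added response option per valve, one changed condition, one descriptive table and an editorial reconciliation. No extra examination is needed. Echocardiograms already read would need a second look only where moderate was entered or the item was left blank.

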#### 6.1.7 *6-Minute Walk Test (6MWT)*

The 6MWT is a practical simple test that requires a 100-ft hallway (30 m) but no exercise equipment or advanced training for technicians. Walking is an activity performed daily by all but the most severely impaired patients. This test measures the distance that a patient can quickly walk on a flat, hard surface in a period of 6 minutes. It evaluates the global and integrated responses of all the systems involved during exercise, including the pulmonary and cardiovascular systems, systemic circulation, peripheral circulation, blood, neuromuscular units, and muscle metabolism. It does not provide specific information on the function of each of the different organs and systems involved in exercise or the mechanism of exercise limitation, as is possible with maximal cardiopulmonary exercise testing. The self-paced 6MWT assesses the submaximal level of functional capacity. Most patients do not achieve maximal exercise capacity during the 6MWT; instead, they choose their own intensity of exercise and are allowed to stop and rest during the test.

Medication taken within the last 12 hours before the test will be documented.

Blood pressure (mm/Hg), heart rate (beats/min), the saturation of peripheral oxygen (SpO2; %), dispnoe and fatigue assessed by Borg scale and the occurrence of any heart rhythm disturbances (if yes, slight to moderate or severe?) will be documented before

starting the test and at the end of the test. In case of severe heart rhythm disturbances patient must not perform 6MWT!

Borg scale:

|                         |                        |
|-------------------------|------------------------|
| 0 = nothing at all      | 5 = severe (heavy)     |
| 0.5 = very, very slight | 6                      |
| 1 = very slight         | 7 = very severe        |
| 2 = slight              | 8                      |
| 3 = moderate            | 9                      |
| 4 = somewhat severe     | 10 = very, very severe |

The documentation of the test performance includes reasons for stopping or early termination of the test and the total distance walked within 6 minutes.

The 6MWT will be performed in accordance with the Schedule of Assessments (Table 2; Screening, Hospital Discharge, 6-Month Follow-Up;) and will be documented in the CRF.

## 6.2 Quality Of Life Questionnaires

QoL will be assessed using the Short Form Questionnaire (SF-36) and Minnesota Living with Heart Failure Questionnaire (MLHF-Q) and additionally a standardized questionnaire for clinical and economic appraisal, the EQ-5D. These assessments will be performed in accordance with the Schedule of Assessments (Screening, 3-Month Follow-Up, 6-Month Follow-Up, 24-Month Follow-Up; Table 2).

### 6.2.1 Short Form Questionnaire (SF36)

The Short Form QoL questionnaire with 36 questions is a well-documented, self-administered scoring system measuring health status. It is used to measure subtle changes in health that follow medical interventions, such as surgery, and in allowing comparison of one technique against another (see Appendix ).

### 6.2.2 Minnesota Living With Heart Failure Questionnaire (MLHF-Q)

The Minnesota Living with Heart Failure Questionnaire (MLHF-Q) is a disease specific instrument which is composed of 21 items and three scales that measure the following (see Appendix ):

- The physical functioning dimension (8 items)
- The emotional functioning dimension (5 items)
- The overall score on health-related QoL (8 items).

### 6.2.3 Questionnaire of the EuroQoL group: EQ-5D™

EQ-5D is a standardized measure of health status developed by the EuroQol Group in order to provide a simple, generic measure of health for clinical and economic appraisal. (User guide v3 April 2010). The EQ-5D essentially consists of 2 pages - the EQ-5D descriptive system and the EQ visual analogue scale (EQ VAS).

The EQ-5D descriptive system comprises the following 5 dimensions: mobility, self-care, usual activities, pain/discomfort and anxiety/depression. Each dimension has 3 levels: no problems, some problems, extreme problems.

### 6.3 Safety Parameters

#### 6.3.1 *Adverse Events (AEs)*

##### 6.3.1.1 *Definitions*

###### 6.3.1.1.1 Adverse Events

Any untoward medical occurrence in a patient or clinical investigation subject administered a pharmaceutical product and which does not necessarily have a causal relationship with this treatment is defined as an AE. An AE can therefore be any unfavorable and unintended sign (including an abnormal laboratory finding), symptom, or disease temporally associated with the use of an investigational medicinal product (IMP), whether or not related to the IMP.

